#### (1) Room design and clinical considerations in resource planning

Room design incorporated the aggregation of patients with delirium and difficult to control behaviours in a single 5-bedded cubicle. In Singapore, a multi-bedded system is common and hence would not cause additional concerns to patients and caregivers. Specific elder-friendly considerations include: 1) card access door; 2) low hospital beds; 3) individual night light; 4) falls modification in the toilet with movement-activated sensor lighting; 5) large wall clock; 6) calendars and 7) headboards indicating sensory impairments (if present), patient's favourite hobbies or activities to aid in individualised activity sessions. Other features of the GMU room include adequate lighting, panic button to ensure staff safety (in event of unpredictable combative patient behaviour) and a central space for group activities.

We aimed to provide higher nursing ratio of 1 trained nursing staff to 2.5 patients. The trained nurses, without distraction from other nursing and patient issues, are able to devote full attention to monitor the conditions of the 5 patients in the GMU and thereby able to initiate early interventions should they detect any deterioration in condition. This form of set up will ensure the reduction of the likelihood of injuries, falls and also allow active and early intervention to prevent functional decline and deterioration of the condition.

#### (2) GMU specific program and core interventions

The following program interventions were implemented by the multi-disciplinary team:

(1) Family orientation upon patients entering the GMU (with a standardised information sheet translated in all 4 languages with regards to the aims and interventions in the GMU). Family members are encouraged to visit patients daily to encourage communication and social support to the patients (Daily Visitor program).

(2) Geriatric nursing assessment and interventions (specific nursing assessment and interventions for cognitive and functional impairment, dehydration, nutrition, psychoactive medication use and discharge planning).

(3) The nurses involved in this program underwent a series of in-service training sessions with regards to the interventions including training on administration of cognitive screening tests and delirium scales; non-pharmacological and pharmacological management of delirium; delirium care and one-on-one interactions; communication skills in counseling concerned family members; psychogeriatrician teaching stress management skills; with support from the geriatric ward level nursing managers as well as cognition nurse clinicians who will counsel and aid in on-site difficult-to-manage behaviours. A pre- and post-implementation questionnaire of delirium knowledge was administered (table 2).

**Table 2 T2:** Delirium knowledge questionnaire administered to staff of geriatric ward pre- and post- GMU implementation

	Knowledge Questions
1	Physical and/or chemical restraints used on a patient with delirium will protect them from harming themselves.
2	Patients with delirium will always present with agitation or restlessness.
3	We would be able to identify if the patient has delirium by administering the Abbreviated Mental Status Test (AMT).
4	Light therapy is beneficial in delirium management
5	Reality orientation can help in re-orientating the patient with delirium.
6	Dementia is the long term complication of delirium.
7	The first line management when a patient is unable to sleep is the use of a benzodiazepine (such as diazepam, lorazepam).
8	Delirium usually goes away immediately after the medical treatment is given.
9	Ensuring that the patient is well hydrated is an important factor in reducing delirium.
10	Confusion and delirium is part of normal aging.
11	The elderly patient may present with atypical symptoms that complicate the diagnosis of delirium.
12	Patients with functional decline will not benefit from early rehabilitation.

(4) Reference resources and practical reminders were made available for the staff in GMU.

(5) A continuing education program for care providers was implemented where the staff (doctors, allied health staff) involved in the GMU has regular training to increase awareness and knowledge in diagnosis and management of delirious patients.

(6) Nursing leaders helped support the trained nurses during the implementation stage.

(7) Daily geriatrician input with regards to these patients with daily documentation of mental status (Abbreviated Mental Status Test (AMT)/Chinese Mini Mental State Examination (CMMSE)) [37,38], Confusion Assessment Method (CAM) questionnaire [39] and type and severity of delirium (hyper-, hypo- or mixed delirium), Delirium Rating Scale (DRS) - severity [40], type of restraint use (physical and chemical including documentation of indication for restraint), pain assessment and medication management.

(8) Twice-weekly multidisciplinary rounds (involving the geriatricians, cognition nurse clinician, nurses, physiotherapists, occupational therapists, case coordinator, pharmacist, medical social worker, and dietician).

(9) Monthly meetings with the multidisciplinary staff members to evaluate the ongoing program, refine, voice out problems

(10) Early involvement of care co-ordinator or medical social worker (where appropriate) in discharge planning.

GMU core interventions are performed daily (see Table 3) and incorporated via a structured protocol into the daily nursing workflow and documentation sheet.

**Table 3 T3:** GMU Core interventions

1.	No mechanical restraints and where possible, no pharmacological restraints. After trying all non-pharmacological methods and patient proves to be a danger to himself and others, then antipsychotics and sedative-hypnotics are used carefully at the lowest possible dose and to tail down the dose and remove the pharmacological agent once not required.
2.	Thrice daily patient orientation via reality orientation board
3.	Early mobilization with the help of therapists and trained nurses
4.	Provision of visual aids (such as eye glasses) if available
5.	Providing adequate hearing aids/earwax disimpaction where necessary with the use of portable audio amplifier
6.	Oral volume repletion/feeding assistance with scheduled oral intake schedule
7.	Sleep enhancement using non-pharmacological sleep protocol of warm milk, relaxation tapes or music. Sedative-hypnotic agents will again be the last line management.
8.	Bright light therapy from 6-10 pm
9.	Thrice daily therapeutic activities program for cognitive stimulation and socialization
10.	Minimizing immobilizing equipments like intravenous drip, urinary catheter, oxygen tubing
11.	Daily visitor program by family to encourage communication and social support
12.	Pain management

*These core interventions was then developed as standardized protocol and incorporated into the usual nursing assessment and daily documentation sheet by way of a checklist.

#### (3) Bright light therapy

Considerations in GMU design also included provision of a controlled environment with bright light therapy built into the room lights. Contributing factors to exacerbating delirium are changing physical environment and unfamiliarity of staff to the needs of delirious patients. The GMU is able to provide a controlled setting with minimal changes to the environment and nurses attending to them. In addition, bright light therapy will be carried out in this room from 6 pm to 10 pm (brightness of approximately 2000 to 3000 lux). The aim of bright light therapy is to establish healthy sleep-wake cycle with appropriate timing set to a desired phase. Since sleep deprivation is one of the contributing factors to worsening delirium, it will be beneficial to place such patients in this room to modulate their sleep-wake cycle. The peaceful environment, free from the movement and noises from other patients will allow better and uninterrupted period of sleep.

##### Inclusion, exclusion criteria and patient transfers

The admission criteria for GMU included patients above age of 65 years old assessed to have delirium (either on admission or incident delirium during hospital stay) who were admitted to the geriatric medicine department. Patients were excluded if they had medical illnesses which require special monitoring (e.g. telemetry for arrhythmias or acute myocardial infarction); were deemed to be dangerously ill, in coma or had terminal illness; uncommunicative patients or patients with severe aphasia; severely combative behaviour with high risk of harm; and patients with mania or other severe eye disorders and other contraindications to bright light therapy (such as patients on photosensitising medications). Finally we also excluded patients with respiratory or contact precautions, or there was verbal refusal of GMU stay by family/patient/physician-in-charge.

The GMU will have a dynamic system for transfers (akin to an intensive care unit) whereby patient flow is effected once they are assessed to have met entry or discharge criteria. This will be based upon both subjective and objective approach when the medical team deems the patients to have easy to manage behaviour/minimal or stable behavioural medications and objectively supported by decreased severity of delirium, based on DRS and CAM-severity scores.

##### Study design and patients recruitment

Our study consist of a pre/post GMU implementation as well as concurrent GMU patients versus patients with delirium managed in the geriatric ward as controls. We will collect available data for patients with delirium admitted to the geriatric department one month prior to GMU implementation. We will give a one-month run-in period after establishment of GMU to smoothen out the initial teething issues and operational issues. The study recruitment commenced in November 2011. We will subsequently identify patients with delirium who meet the inclusion and exclusion criteria for GMU. Using Zelen's method of randomization [41,42], we will admit the patients to GMU and assign others to the control group (see Figure 1). The geriatric team managing the patients in both groups will speak with family regarding the study and if agreeable, consent with be obtained by the GMU co-ordinator and/or geriatric team.

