**Methods/Design:**

GMU models after the Delirium Room with adoption of core interventions from Hospital Elder Life Program and use of evening bright light therapy to consolidate circadian rhythm and improve sleep in the elderly patients. The novelty of this approach lies in the amalgamation of these interventions in a multi-faceted approach in acute delirium management. GMU development thus consists of key considerations for room design and resource planning, program specific interventions and daily core interventions. Assessments undertaken include baseline demographics, comorbidity scoring, duration and severity of delirium, cognitive, functional measures at baseline, 6 months and 12 months later. Additionally we also analysed the pre and post-GMU implementation knowledge and attitude on delirium care among staff members in the geriatric wards (nurses, doctors) and undertook satisfaction surveys for caregivers of patients treated in GMU.

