**Morbidity and mortality**	**Rate of falls** **Physical injuries** **Urinary catheter usage** **Pressure ulcer development** **Rate of nosocomial infections** **Inpatient mortality**	X	X	X
**Qualitative measures**	**Family satisfaction survey** **Staff satisfaction survey** **Staff knowledge survey**	-	X	X
**Follow-up data (6, 12-monthly)**	**Rate of hospitalization** **Functional status (BI)** **Institutionalisation** **Mortality**	-	X	X

The primary outcome measures we will look at include: (i) Clinical data with regards to duration and severity of delirium; frequency of use of physical restraints, use of pharmacological agents/sedative hypnotics, physical injuries or monthly falls rates; and nosocomial infection rates (ii) Functional outcomes by way of modified Barthel Index score and (iii) Patient/family satisfaction score; all adjusted for baseline demographics and comorbidities. We aim to look at the outcomes measures of patients with delirium admitted to GMU versus those managed under usual care (control group)(refer to Figure 1).

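### Concurrent controls share the geriatric ward, and apparently the team, with the GMU, so carry-over could shrink the main contrast; no direct pre-GMU v concurrent-control check is named in the visible text

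*Protocol article*

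**What the plan says.** Under Study design and patients recruitment, the article sets out two patient contrasts: "Our study consist of a pre/post GMU implementation as well as concurrent GMU patients" against controls from the geriatric ward. The second of these reads in full "concurrent GMU patients versus patients with delirium managed in the geriatric ward as controls". The concurrent patients are those who meet the GMU inclusion and exclusion criteria, allocated by Zelen's method after a one-month run-in. The earlier cohort is described differently: "We will collect available data for patients with delirium admitted to the geriatric department one month prior to GMU implementation". The same section says that "The geriatric team managing the patients in both groups will speak with family regarding the study", which points to shared clinicians.

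The staff component covers the geriatric wards as a whole. The Abstract (Methods/Design) says the study analysed "pre and post-GMU implementation knowledge and attitude on delirium care among staff members in the geriatric wards (nurses, doctors", and Table 2 is titled "Delirium knowledge questionnaire administered to staff of geriatric ward pre- and post- GMU implementation". The Abstract's Discussion paragraph hypothesises better staff knowledge. Training is described more narrowly: in-service sessions for nurses in the programme, and a continuing education programme in which doctors and allied health staff involved in the GMU "has regular training to increase awareness and knowledge in diagnosis and management of delirious patients".

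The only patient outcome comparison spelled out under Data collection is "We aim to look at the outcomes measures of patients with delirium admitted to GMU versus those managed under usual care". The sample size section assumes a 10-point Barthel difference with no allowance for a smaller contrast.

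**The concern.** The design hopes that knowledge of delirium care improves among geriatric ward staff, and it draws its usual-care group from that ward over the same period. If better knowledge or shared clinicians change how controls are treated, usual care moves part of the way towards the GMU package, and the randomised difference shrinks even if the package works.

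A small or null difference would then have two explanations: the GMU adds little, or the control ward has already taken up part of it. The distinction matters because the authors hope to transfer the model to other wards. A pre-GMU cohort of 50 is being collected and could help to separate the two explanations, but the visible text does not say how it would be used for that purpose.

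**Working it through.** **1. Reproduce the planned sample size.** Inputs from Sample size and statistical analyses: difference 10, SD 14, ratio 1, 90% power, 5% significance, 45 per group, 10% loss. Sidedness is not stated; two-sided is assumed.

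- Normal approximation: n = 2 × (1.960 + 1.282)² × 14² / 10² = 41.2, so 42 per group. The t-based value is 43.
- At 45 per group the t-based power is 91.8%.
- Loss to follow-up: 45 / (1 − 0.10) = 50.

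The planned 45 is slightly conservative and not in error.

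**2. What carry-over would do.** If a share c of the 10-point benefit also reaches controls, the contrast is 10 × (1 − c). The document gives no value for c, so the shares below are assumptions. Power is t-based at 45 per group with SD 14; the last column is the normal-approximation n per group for 90% power, before dropout.

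| Share c | Contrast (points) | Power at 45 | n per group for 90% |
|---|---|---|---|
| 0% | 10 | 91.8% | 42 |
| 10% | 9 | 85.5% | 51 |
| 20% | 8 | 76.5% | 65 |
| 30% | 7 | 65.0% | 85 |
| 50% | 5 | 38.8% | 165 |

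**3. Which components could carry over.** From Table 3, these could be copied on an ordinary ward: orientation, early mobilisation, the non-drug sleep protocol, fewer catheters and drips, and drug minimisation. These could not: the five-bed room, the light therapy built into its lighting, and the nursing ratio of 1 to 2.5. Any carry-over is therefore likely to be partial.

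**4. What the stated contrasts can show.** For a measure collected in all three groups, (GMU − pre) − (GMU − control) = control − pre. The two stated contrasts together therefore imply the drift in usual care, though no comparison of control with pre is named. Table 4 marks restraint records, medications, catheter use and the modified Barthel Index in all three columns. It does not mark CAM severity, DRS-98 or the 6- and 12-month follow-up for the pre-GMU column, so drift cannot be examined on those.

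**5. How precise a Barthel check would be.** With 50 v 50 and SD 14, the 95% half-width is 1.984 × 14 × √(2/50) = 5.6 points. Power is about 11% for a 2-point drift and 42% for a 5-point drift. Modest drift would usually be missed on this scale, which is why care-process items are the better choice.

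**6. Comparability of the cohorts.** Concurrent patients must meet the GMU criteria, which exclude, among others, the dangerously ill, those needing special monitoring, the severely combative and those under infection precautions. The text does not apply these limits to the pre-GMU cohort. A difference between that cohort and either later group therefore mixes case-mix with care.

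**The case against.** A reader might infer that success on the staff objective necessarily erodes the main contrast. The documents do not support that. Formal training is described only for staff involved in the GMU, and surveying ward staff is not the same as training them. The room, light and staffing cannot spread. The article's Discussion also reports that staff already knew the core interventions helped but did not put them into practice, so a gain in knowledge need not change care. Improved staff knowledge is a stated hypothesis but is not listed among the primary or secondary aims in the Background.

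A reader might also infer that nothing in the plan would reveal drift. That is too strong: the identity in step 4 recovers it indirectly, and the pre/post staff survey could show a rise in knowledge. Figure 1, on study design and allocation, is not shown and may name further comparisons. Supportive analyses are often left to a fuller document.

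These points limit the concern to a risk of unknown size. They do not remove the shared setting, the wording about a single team, or the lack of an eligibility limit on the pre-GMU cohort. Those are features of the design as published. The Discussion's remark also cuts both ways: a programme meant to close the gap between knowledge and practice could close it for controls too.

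**Conclusion.** The point stands as a plausible source of dilution and an avoidable weakness in the supporting comparison. It does not invalidate the randomised contrast. If the transferable components help patients and part of their effect reaches controls, the GMU v control difference is biased towards zero. The illustrative cost is a fall in power from 91.8% to 76.5% for a 20% loss of contrast, with 85.5% at 10% and 38.8% at 50%. These figures rest on the protocol's SD of 14, 45 per group, a two-sided 5% test and assumed shares.

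It would be tempting to treat the concurrent difference as a lower bound on the effect against pre-GMU care. That is not established: it would depend on a non-randomised comparison across calendar time.

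**What to change.** - Restrict the pre-GMU cohort to patients meeting the GMU inclusion and exclusion criteria, as far as the available data allow, and state which criteria could not be applied. This also makes the stated pre/post contrast compare like with like.
- Prespecify a supportive pre-GMU v concurrent-control comparison on the care-process items Table 4 marks for both: restraint records, antipsychotic and benzodiazepine use, and catheter use. Adjust for baseline demographics and comorbidity, as already planned for the primary outcomes.
- State in advance that, if controls have shifted towards GMU practice, the randomised difference will be described as GMU v contemporaneous, possibly enhanced, usual care, without claiming a proven lower bound.
- Report post-implementation staff knowledge separately for GMU staff and for staff caring only for controls. At the same time, reconcile Table 4, which shows no staff knowledge survey in the pre-GMU column, with the Abstract and Table 2, which describe one.

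The cost is one extra planned comparison on data already collected, an eligibility screen of the pre-GMU records, and a work-location field on the questionnaire. The screen may reduce the pre-GMU cohort below 50. The check remains non-randomised, confounded by calendar time and limited to one pre-GMU month. On the Barthel Index it is precise only to about ±5.6 points, so it can inform interpretation but not settle it.

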##### Data collection

Table 4 summarizes the parameters and outcomes of interest. Data that will be collected include patient demographics (age, gender, race, length of hospital stay, duration of delirium(days); comorbidity and severity of illness data using modified Charlson's comorbidity index [43] and modified severity of Illness index [44]. Cognitive status will be assessed by way of the locally validated cognitive screening instrument (Abbreviated Mental Status Test (AMT)) [37] and functional status (using modified Barthel Index) [45] during the initial and pre-discharge phase of patient's admission. This was administered by a single trained assessor. We also aim to look at the rate and duration of physical restraint and frequency of chemical restraint use. To adjust for the differences antipsychotic usage, we will use chlorpromazine equivalence [46] to look at the total antipsychotic usage during the admission, as well as frequency of antidepressant and benzodiazepine use. Rate of falls and physical injuries, urinary catheter usage, complications of immobility (pressure ulcer) and rate of nosocomial infections will be systematically collected during patient's hospital stay. The functional outcomes in the geriatric patients with delirium include follow-up phone interview at baseline, 6 months and 12 months later. Hospitalisation, morbidity and mortality data over the same follow-up period will also be collected during those time intervals. These data will be obtained from patients in the GMU patients and usual care (control group). We will assess family/caregiver satisfaction via surveys conducted for loved ones of delirious patients in GMU versus those whom are receiving usual care.

**Table 4 T4:** Overview of assessments used in GMU implementation study

Domain	Type of assessment/Outcomes			
		Pre-GMU implementation	GMU implementation	GMU concurrent controls
**Baseline demographics**	**Age, race, gender, length of hospital stay**	X	X	X
**Cognition**	**AMT** **CMMSE**	X -	X X	X X
**Comorbidity**	**Charlson's index** **SIRS**	X X	X X	X X
**Delirium severity**	**CAM severity score** **DRS-98**	- -	X X	X X
**Functional status**	**Modified BI**	X	X	X
**Physical restraints**	**Daily records**	X	X	X
**Medications**	**Antipsychotics (chlorpromazine equivalence)** **Antidepressants** **Benzodiazepines**	X	X	X

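### As written, the pre-GMU cohort is not held to the GMU eligibility criteria and lacks several outcomes, so the pre/post comparison is open to selection bias and should be supportive only

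*Protocol article*

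**What the plan says.** The section on study design and patient recruitment sets up two comparisons: "Our study consist of a pre/post GMU implementation as well as concurrent GMU patients versus patients with delirium managed in the geriatric ward as controls". The sample size section plans 50 pre-implementation, 50 GMU and 50 control subjects.

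The cohorts are described in different terms:

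- **Before the GMU:** "We will collect available data for patients with delirium admitted to the geriatric department one month prior to GMU implementation".
- **After a one-month run-in:** "We will subsequently identify patients with delirium who meet the inclusion and exclusion criteria for GMU". These patients are then divided between GMU and control.

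The criteria themselves stand in the section on inclusion, exclusion and transfers, where they are presented as admission criteria for the GMU. Patients are left out if they "were deemed to be dangerously ill, in coma or had terminal illness; uncommunicative patients or patients with severe aphasia", and also for "severely combative behaviour with high risk of harm", for respiratory or contact precautions, for a need for special monitoring, for contraindications to bright light, or where "there was verbal refusal of GMU stay by family/patient/physician-in-charge".

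Table 4 lists what is collected in each group. In its delirium severity row ("CAM severity score" and DRS-98) the pre-GMU column holds only dashes. The rows for surveys and for 6- and 12-month follow-up also show a dash there. The data collection section says that the primary outcomes will be adjusted for baseline demographics and comorbidities, and that GMU patients will be compared with usual-care controls.

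**The concern.** A before/after comparison is interpretable only if the same kind of patient stands on both sides. Here the later side is filtered and the earlier side, as described, is not. The filter bears on the outcomes being compared. Severe combativeness bears on restraint use, antipsychotic use and injury. Dangerous illness, coma and terminal illness bear on inpatient death, pressure ulcers and Barthel score. Isolation status may bear on infection. If such patients stay in the earlier cohort and are removed from the later one, a change in case mix could be read as a benefit of the unit.

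The second issue is coverage. A reader of the design statement could expect pre/post evidence on all the primary measures, but the earlier cohort has no data for some of them.

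**Working it through.** **1. Eligibility, side by side**

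| Item | Pre-GMU cohort | GMU and concurrent control |
|---|---|---|
| Source | Delirious patients admitted to the geriatric department | Delirious patients identified after the run-in |
| GMU inclusion and exclusion criteria | Not mentioned | Stated to apply |
| Refusal of GMU stay | Cannot occur, as no unit exists yet | Excludes the patient |

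The article does not say that the criteria are waived for the earlier cohort. It does not apply them either, and one of them could not have applied.

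**2. What adjustment can reach**

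Table 4 marks age, race, gender, AMT, Charlson's index, SIRS and modified Barthel for the earlier cohort. Adjustment for demographics and comorbidity may therefore remove part of a case-mix difference. Combativeness, terminal status and isolation status are not named as covariates. Delirium severity cannot serve as one, because it is not collected before the GMU.

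**3. Coverage of the seven primary groups listed at the end of the Background**

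| Primary group | Pre-GMU column of Table 4 |
|---|---|
| 1. Delirium duration and severity | Severity not collected; duration has no row |
| 2. Physical and chemical restraints | Collected |
| 3. Falls | Collected |
| 4. Physical injury | Collected |
| 5. Function | Modified Barthel collected, but no 6- or 12-month value |
| 6. Morbidity (infection, catheter, pressure ulcer) | Collected |
| 7. Satisfaction | Not collected |

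Five of seven groups (2 to 6) have in-hospital data. Severity, satisfaction and all follow-up outcomes, including Barthel at one year, are out of reach for pre/post.

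**4. The plan's own figure**

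The sample size uses a Barthel difference of 10, SD 14, 90% power and 5% significance (two-sided assumed), for GMU versus control.

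- Normal approximation: n = 2 × (1.960 + 1.282)² × 14² / 10² = 41.2, so 42 per group.
- Two-sample t-test: 42.2, so 43 per group. The stated 45 is within two of this and gives 91.8% power.
- Loss of 10%: 45 / 0.9 = 50, as stated.

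The figure is sound for its purpose, but it sizes the concurrent comparison and not pre/post.

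**5. Illustration of the selection effect**

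These inputs are assumptions and do not come from the article. A share f of the pre-GMU cohort would have failed the GMU criteria, and their Barthel score is lower by d points. There is no true effect and no adjustment. The groups are 50 pre-GMU and 50 GMU patients, with the plan's SD of 14 (ignoring the extra spread from mixing).

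- Bias = f × d.
- Standard error = 14 × √(2/50) = 2.8.
- Chance of a significant result favouring GMU = 1 − Φ(1.96 − bias/2.8). It is 2.5% when there is no bias.

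| f | d | Bias (points) | Chance |
|---|---|---|---|
| 10% | 10 | 1 | 5% |
| 20% | 20 | 4 | 30% |
| 30% | 30 | 9 | 90% |

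The range runs from negligible to decisive. The article gives nothing that would narrow it.

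**The case against.** The best defence is that little rests on pre/post. The primary aim, the outcome statement and the sample size all concern GMU against usual care, and both of those groups come from patients who meet the same criteria. That stands, and it limits the point to the pre/post component. Even so, the design statement names that component and a third of the planned subjects serve it.

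A second defence is that silence is not waiver. This is a condensed article, Figure 1 is not available, and chart-selection rules may stand in a fuller document. It is fair to call the missing restriction an inference from the wording. Yet the article does say who enters each cohort, and the two descriptions differ. The adjustment defence also counts in part, since comorbidity and baseline measures exist for the earlier cohort.

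Some stronger readings are tempting but unsupported:

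- *Pre/post cannot address most primary outcomes.* Table 4 shows in-hospital data for five of seven groups.
- *The earlier cohort has no delirium measures at all.* Only severity is shown as absent. Duration is in the data collection list without a Table 4 row, so its availability is simply not stated.
- *Every outcome must look better after the GMU.* Comatose or dangerously ill patients need not fall more or be restrained more, so bias on those outcomes could run either way.
- *The 50 are picked without a rule from about 300 in the month.* The Background's 3,600 patients a year would give 3,600 / 12 = 300, but it is offered only as a potential figure. With the quoted 15-day stay it implies 3,600 × 15 / 365 = 148 delirious inpatients at once. At 15% prevalence that is about 148 / 0.15 ≈ 986 occupied beds, which is hard to read as one department. The month may hold far fewer cases.

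**Conclusion.** The point holds for the pre/post comparison only. Taken as written, that comparison sets an unrestricted delirium cohort against one filtered by illness severity, behaviour and isolation status. Restraint use, injury, infection, pressure ulcers, function or inpatient death could therefore appear to improve without a GMU effect. The conclusion assumes that the text means what it says about who enters the earlier cohort. The size of the bias, and its direction for each outcome, cannot be derived from the article; the Barthel scenarios only show that it could matter at 50 per group. The absence of severity, satisfaction and follow-up data before the GMU is not an assumption, since Table 4 shows it. The change is worth making because it is specific and cheap, but it does not put the study's main comparison in doubt.

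**What to change.** 1. State that the GMU inclusion and exclusion criteria apply to the pre-GMU month as far as charts support them. Refusal of GMU stay cannot apply there, so acknowledge it as a remaining difference.
2. Take consecutive eligible patients up to 50. If fewer are found, analyse the eligible subset.
3. State that pre/post is supportive only and limited to the in-hospital outcomes that Table 4 marks for that period: restraints, medication, falls, injury, Barthel, catheter use, pressure ulcers, infection and inpatient death. State also whether delirium duration is available.
4. Rest the conclusions on GMU versus concurrent control.

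The cost is chart screening of one month, a few sentences of text and possibly fewer than 50 pre-GMU patients. The sample size calculation does not change, because it rests on the concurrent groups.
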